### Post-intervention interviews

MSC-LC participants will be invited to participate in post-intervention interviews to provide a deeper understanding of their experiences with the intervention and to capture aspects of its impact that may not be reflected in the quantitative assessments [65]. Participants in the MSC-LC condition who completed at least one intervention session will be invited to complete individual semi-structured interviews (45–60 min) conducted virtually by a trained study team member. Each interview will be audio-recorded, transcribed verbatim, and de-identified. The interview guide is designed to elicit feedback across several domains, including intervention acceptability (e.g., perceived appropriateness of intervention content, satisfaction with the intervention), reflections on the intervention and its impact, motivation and engagement factors influencing retention, group dynamics, intervention content and its tailoring to lung cancer, program structure and delivery mode, and suggestions for improvement.

### Data analysis

#### Quantitative analyses

Range checks will be conducted to identify missing, aberrant, or out-of-range values, which will be reviewed and resolved by the study team. Descriptive statistics (means, standard deviations, frequencies) will be reported for all study variables, and zero-order correlations will be examined to assess associations among outcomes and mediators. Key clinical characteristics (e.g., disease stage, smoking history) will be described across study arms and explored in relation to primary outcomes (e.g., session attendance) to inform future trial design. Analyses will be conducted using Stata v19.

The primary outcomes of interest are feasibility and acceptability indices; clinical and psychosocial outcomes will be considered secondary exploratory outcomes. Progression criteria were established a priori to classify outcomes as feasible, in need of amendment, or not feasible based on predefined thresholds. Feasibility will be evaluated using descriptive statistics. The intervention will be considered feasible to deliver if at least 60% of participants in the MSC-LC condition attend six or more sessions, reflecting meaningful engagement while accounting for common attendance barriers in oncology populations; it will be considered not feasible if 33% or fewer meet this threshold. Recruitment will be considered feasible if at least 50% of eligible participants (with lung cancer diagnosis confirmed via medical record) agree to enroll and be randomized, and not feasible if recruitment uptake is 33% or less. Retention will be considered feasible if at least 70% of participants remain in the study through the post-intervention assessment and not feasible if 50% or fewer are retained. Treatment fidelity adherence will be considered adequate if ≥80% of predefined intervention components are delivered per session, ensuring that the intervention is delivered with sufficient integrity, and not considered feasible if fidelity adherence is 50% or less. Fidelity via interventionist competence will be deemed sufficient if the mean MSC TAC rating across the three sampled sessions per cohort and per interventionist is greater than or equal to 4 (“competent”) with no individual domain less than 3 (“advanced beginner”). We will also report the proportion of ratings at or above 5 (“proficient”) as an indicator of intervention quality.

As this is a pilot trial designed to assess feasibility and explore preliminary signals of intervention effects, analyses of patient-reported outcomes will be descriptive and exploratory, based on available data. For each patient-reported outcome, we will report descriptive statistics and 95% confidence intervals, where relevant, at each assessment timepoint (baseline, mid-intervention, post-intervention, follow-up) separately by group. For interpretability, we will also report the proportion of participants at each timepoint who meet or exceed suggested clinical cutoffs for select measures (e.g., LCSI ≥ 38, PHQ-8 ≥ 10, GAD-7 ≥ 10), as well as the proportion demonstrating clinically meaningful change (e.g., moving from above to below threshold). These findings will be used to refine theory-driven hypotheses and inform analytic strategies for a future trial. Exploratory analyses of potential mechanisms (e.g., changes in mindfulness, loneliness) will not be formally modeled in this pilot trial; however, descriptive patterns in these hypothesized mediators will be reported.

No interim analyses or formal stopping rules are planned given the exploratory and pilot nature of the trial. The PI will make the final decision regarding early study termination in consultation with the IRB if safety concerns or unanticipated issues arise. Given the small sample size, statistical models will be applied in an exploratory manner to examine patterns of change. Exploratory effect size estimates will be reported to inform variance estimation and plausible effect size ranges for planning a future definitive trial, rather than to evaluate efficacy [66]. Estimates will be interpreted cautiously, recognizing that the stability of effect sizes is limited in this pilot study context. Missing data will be summarized descriptively (extent and patterns across assessment timepoints) to contextualize and interpret feasibility outcomes. Findings will be used to refine hypotheses and analytic strategies for subsequent, adequately powered trials.

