### Aims of the current study

The primary aim of this pilot RCT is to evaluate the intervention feasibility and treatment fidelity and acceptability of the MSC-LC program in adults with lung cancer who report clinically elevated stigma. The target for trial feasibility is 50% of eligible participants agreeing to enroll in the study and be randomized (recruitment), 30% attrition or lower (retention), and 60% of participants in the MSC-LC condition attending six or more session (attendance). The target for treatment fidelity is >80% of intervention components deliver per session (interventionist adherence to protocol) and average intervention delivery competency ratings greater than or equal to 4 out of 6 (indicating “competent” delivery) using a standardized assessment. Acceptability will be evaluated through qualitative feedback on appropriateness and satisfaction of the MSC-LC intervention.

This pilot trial will also explore whether MSC-LC is associated with improvements in lung cancer stigma, self-compassion, depressive symptoms, anxiety, and spiritual well-being (secondary outcomes), and examine theory-driven mechanisms of change. In addition, we will conduct post-intervention qualitative interviews with participants to identify salient experiences, mechanisms of change, and areas for refinement not captured in quantitative outcomes.

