After providing signed informed consent, participants will be randomized to either the MSC-LC or CTL condition. Prior to randomization, a randomized allocation sequence will be generated using the NCI Clinical Trial Randomization Tool [36]. Parameters for generating the allocation sequence include an asymptotic maximal randomization method, a maximum tolerated imbalance of 2, and an allocation ratio of 1:1 without stratification. Randomization will not be stratified in this pilot study, informed by formative qualitative findings indicating participant preference for heterogeneous group composition and expert guidance emphasizing the importance of shared emotional experiences across varying clinical contexts (e.g., disease stage, treatment) within the MSC-LC intervention [14]. To prevent selection bias, the research staff is provided with a participant’s allocation only after that participant has provided informed consent and has been accepted into the trial. Because the MSC-LC intervention is delivered in group format, randomization occurs prior to baseline assessment to allow for scheduling alignment among those assigned to the intervention group. Due to the nature of the behavioral intervention, participants and interventionists cannot be blinded to condition assignment.

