### Sample size justification

Consistent with methodological guidance that pilot trial sample size should be large enough to estimate key feasibility parameters with acceptable precision, minimum sample size was determined based on feasibility objectives and progression criteria rather than testing for intervention efficacy [38].

A priori progression criteria were defined for recruitment, retention, session attendance in the MSC-LC condition, and treatment fidelity. Recruitment will be considered feasible if at least 50% of eligible participants enroll and not feasible if recruitment uptake is 33% or less. Retention will be considered feasible if 75% or more of participants complete follow-up assessments and not feasible if retention is 50% or less. MSC-LC attendance will be considered feasible if at least 60% of participants attend six or more sessions and not feasible if 33% or fewer attend six or more sessions. Treatment fidelity will be considered feasible if at least 80% of intervention components are delivered per session and not feasible if delivery is 50% or less. Using the normal approximation method for a two-arm parallel design with one-sided *α* =.05 and 90% power to evaluate these feasibility thresholds [38], the *minimum* required sample size was *n* = 62 (*n* = 31 per condition).

MSC-LC will be delivered across three planned cohorts, each designed to include approximately 10–15 participants to facilitate meaningful discussion and interpersonal exchange [14, 39]. Accordingly, total recruitment may range from 62 to 90 participants to ensure adequate group size across cohorts. Although the sample size is consistent with accepted conventions for pilot trials, we acknowledge that it limits the precision and generalizability of the quantitative findings. The analyses are intended to inform the design and feasibility of a future fully powered trial.

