#### Intervention feasibility and treatment fidelity (primary outcomes)

Feasibility will be assessed using three indicators, with the number of MSC-LC sessions each participant attends reflecting feasibility of the intervention itself and the number of eligible patients who enroll in the study (recruitment) and the number of questionnaire assessments completed by both MSC-LC and CTL participants (retention) reflecting feasibility of the research protocol for potential scale-up to a larger trial [43]. A priori benchmark indicators to assess feasibility (and treatment fidelity) are listed below in the Data Analysis plan.

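### The retention progression threshold is 75% in the sample size section but 70% in the aims and the analysis plan, so 44 to 46 retained of 62 is classed two ways

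*Protocol article*

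**What the plan says.** All of the following is current text in the protocol article.

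- **Aims of the current study:** the retention target is "30% attrition or lower (retention"), which means at least 70% retained. No timepoint is given.
- **Sample size justification:** "Retention will be considered feasible if 75% or more of participants complete follow-up assessments and not feasible if retention is 50% or less". Which follow-up assessments are meant is not defined. The section then derives a minimum of 62 participants (31 per condition) by a normal approximation with "one-sided *α* =.05 and 90% power to evaluate these feasibility thresholds".
- **Intervention feasibility and treatment fidelity (primary outcomes):** the data source for retention is "the number of questionnaire assessments completed by both MSC-LC and CTL participants (retention"). For the benchmarks themselves, the section sends the reader to the data analysis plan.
- **Quantitative analyses:** "Retention will be considered feasible if at least 70% of participants remain in the study through the post-intervention assessment". The lower limit here is again 50%. The same section explains how the cutoffs are used: "Progression criteria were established a priori to classify outcomes as feasible, in need of amendment, or not feasible based on predefined thresholds".

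**The concern.** The recruitment, attendance and fidelity-adherence cutoffs agree between the sample size section and the analysis section. Only retention differs. Both sections present their criteria as set a priori and both put the lower limit at 50%, so they describe the same rule with two upper limits. Because the plan sorts results into three classes, any retention from 70% to just under 75% is feasible by one section and in need of amendment by the other.

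The endpoint is also unsettled. The analysis section fixes the post-intervention assessment (T3, 10 weeks after baseline). The sample size section leaves its follow-up assessments undefined: they could be T4 at 16 weeks or all post-baseline questionnaires.

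Feasibility is the primary outcome, and the result is meant to inform a larger trial. The article also counts its a priori feasibility standards as a strength. A pass mark with two values weakens that, and it leaves open whether the sample size was derived for the rule that will be applied.

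**Working it through.** **Inputs.** Upper retention threshold 75% (Sample size justification) or 70% (Aims; Quantitative analyses). Lower threshold 50% in both methods sections. One-sided alpha 0.05, 90% power, normal approximation, 31 per condition, recruitment range 62 to 90 (Sample size justification).

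**Step 1: the stated sample size.** For one proportion against a fixed value,

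n = [(z₀.₉₅·√(p0(1−p0)) + z₀.₉₀·√(p1(1−p1))) / (p1−p0)]², with z₀.₉₅ = 1.645 and z₀.₉₀ = 1.282.

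Retention, 75% against 50%: [(0.822 + 0.555) / 0.25]² = 30.35, rounded up to 31. Two arms give 62, which matches the article.

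The same formula for the other pairs of thresholds:

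| Criterion | n | Rounded up |
|---|---|---|
| Retention 70% vs 50% | 49.68 | 50 |
| Attendance 60% vs 33% | 26.93 | 27 |
| Fidelity 80% vs 50% | 19.80 | 20 |
| Recruitment 50% vs 33% | 69.20 | 70 (eligible people, not arm size) |

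One rival match exists. Attendance with a continuity correction gives 30.53, also 31; but with that correction retention at 75% would need 35 (34.24 rounded up), so 31 would not cover every criterion. The 75% retention rule is therefore the likely source of 31, but this is an inference.

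**Step 2: power if 70% is the rule.** Power = Φ{[(p1−p0)·√n − 1.645·√(p0(1−p0))] / √(p1(1−p1))}, with p0 = 0.50 and p1 = 0.70.

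- n = 31 (each arm judged alone): Φ(0.635) = 73.7%.
- n = 62 (both arms together): Φ(1.642) = 95.0%.

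For comparison, 75% against 50% at n = 31 gives 90.6%.

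**Step 3: the disputed band in counts.**

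- N = 62: 70% is 43.4 and 75% is 46.5, so the band is 44 to 46 retained (71.0% to 74.2%).
- N = 90: 70% is 63 and 75% is 67.5, so the band is 63 to 67 retained (70.0% to 74.4%).

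**Step 4: chance of landing in the band (exact binomial).** True retention is not known from the article, so a range is shown.

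| True retention | N = 62 | N = 90 |
|---|---|---|
| 70% | 30% | 40% |
| 72% | 33% | 44% |
| 75% | 30% | 38% |
| 80% | 13% | 11% |
| 85% | 2% | 1% |

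**The case against.** The strongest reply is that the article says where its benchmarks live. The feasibility measures section defers to the data analysis plan, which says 70% through T3, and the aims agree on 70%. On that reading the sample size section is the outlier. This stands, and it limits the point in two ways. A reader might infer that retention is measured in three competing ways, but the count of questionnaires is a data source, not a third rule. A reader might also infer that the pass mark is free to be chosen once the data are in; the pointer to the analysis plan speaks against that, although a contradictory value in print still has to be removed.

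Two further readings go beyond the text. The first is that the trial is underpowered for its retention rule. The 74% figure needs retention to be judged in each arm separately, and no section says so. The criteria are written on participants, and the measures section counts both arms. Read that way, 62 participants exceed the stated 90% power. Feasibility is in any case to be evaluated descriptively.

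The second is that a pooled rule could hide poor retention in the intervention arm and should be required in each arm. A constructed case exists: 29 of 31 controls plus 15 of 31 MSC-LC participants is 44 of 62, or 71%. It has no probability attached, and a separate MSC-LC attendance criterion already watches that arm. A per-arm requirement would be a new and stricter rule. With a 75% cutoff and true retention of 75%, the chance of passing falls from 51% (at least 47 of 62) to 22% (at least 24 of 31 in both arms).

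**Conclusion.** The contradiction is real and needs correction: one primary progression criterion has two upper thresholds, 70% and 75%, and no settled endpoint. Its practical size depends on true retention. Between 70% and 75%, about one trial in three of 62 participants would end in the disputed band; at 85% the conflict would seldom matter (2%). These chances assume independent participants and a rule applied to all 62 together.

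That the sample size rests on 75% is probable, since 75% against 50% reproduces 31 per condition exactly, but the article never names the driving criterion. The endpoint difference is best called an ambiguity: one section fixes T3 and the other is undefined, so a T3 against T4 conflict is not demonstrated. No loss of power is shown if retention is judged on both arms together.

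**What to change.** State one threshold, one endpoint and one denominator in identical words in the aims, the sample size justification and the quantitative analysis section, and let the measures section point to that statement. A workable definition is completion of the T3 assessment among all randomised participants. Then choose one of two routes:

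- **Adopt 75% throughout.** The sample size of 62 stands; the aims and the analysis section change. The cost is a stricter pass mark than the analysis section now has.
- **Keep 70%, as in the data analysis plan.** Restate the sample size justification and say that retention is judged on both arms pooled. On that basis 50 participants are needed in total, and 62 give 95% power. If it were judged per arm, 31 would give only 74%, and 50 per arm (100 in total) would be needed.

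Under either route, name the criterion that drives 31 per condition. Report retention by arm and completion of T4 descriptively, without adding a per-arm pass requirement. The change is wording plus, under the second route, a short recalculation. No new data are needed.

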#### Enhanced standard of care with waitlist control group (CTL)

At present, there are no established clinical guidelines specifically addressing stigma-related distress in individuals with lung cancer. However, the National Comprehensive Cancer Network (NCCN) recommends referral to mental health services for cancer patients experiencing heightened distress. In alignment with these recommendations, participants randomized to the enhanced standard of care with waitlist control group (CTL) will receive an information sheet developed by the National Cancer Institute, which includes guidance on accessing supportive resources and organizations in their community.

Control group participants will also be placed on a waitlist to receive the MSC-LC intervention, and participants are explicitly told they are on a waitlist. Following completion of all scheduled study assessments, they will be offered the opportunity to receive the MSC-LC intervention. This waitlist design ensures that all participants eventually have access to the intervention, while also enabling comparison of the MSC-LC intervention to an enhanced version of current standard care. This approach will allow for rigorous evaluation of whether the MSC-LC intervention provides benefits beyond existing practices for managing distress in people with lung cancer.

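### Retention criterion names no arm: under the 70% cutoff it can be classed feasible while one arm is at or below the plan's own 50% line

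*Protocol article*

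**What the plan says.** Under Data analysis, Quantitative analyses, the protocol article gives the rule: "Retention will be considered feasible if at least 70% of participants remain in the study through the post-intervention assessment". The lower line, at or below which the criterion fails outright, is set at 50%. Results between the two lines are classed as needing amendment. The sentence on attendance in the same paragraph restricts itself to the MSC-LC condition; the retention sentence has no such restriction.

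The section on intervention feasibility and treatment fidelity defines the measure as "the number of questionnaire assessments completed by both MSC-LC and CTL participants (retention". It assigns session attendance to the feasibility of the intervention, and recruitment and retention to the feasibility of the research protocol for a larger trial.

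The aims agree with the 70% figure: "30% attrition or lower (retention". The sample size section does not: "Retention will be considered feasible if 75% or more of participants complete follow-up assessments and not feasible if retention is 50% or less". No section gives a retention cutoff for a single arm or a limit on unequal attrition, and none says how the separate criteria combine into one overall decision.

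**The concern.** The two arms ask different things of participants. MSC-LC has ten weekly 90-minute sessions plus home practice. Controls receive an information sheet and answer questionnaires, and the programme comes afterwards: "Following completion of all scheduled study assessments, they will be offered the opportunity to receive the MSC-LC intervention". Participants know their allocation. Retention could therefore differ between arms, and a single proportion lets good retention in one arm offset poor retention in the other.

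The pilot is meant to inform a larger two-arm trial, where unequal loss would threaten the between-arm comparison. A retention criterion that reads *feasible* while one arm has lost half its participants would not warn of that. The cutoffs are fixed in this article as part of the primary outcome, so how they apply to the arms is not a detail that can be assumed to sit elsewhere.

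**Working it through.** **Inputs.** Cutoffs of 70% and 50% (Quantitative analyses); the alternative 75% and 50%, with "one-sided *α* =.05 and 90% power to evaluate these feasibility thresholds" and "required sample size was *n* = 62 (*n* = 31 per condition" (Sample size justification); recruitment of 62 to 90 (same section); 1:1 allocation with a maximum tolerated imbalance of 2 (section on recruitment and randomization).

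**1. The plan's own figure.** One-sample normal approximation:

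n = [(z₀.₉₅·√(p₀(1−p₀)) + z₀.₉₀·√(p₁(1−p₁))) / (p₁−p₀)]²

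With p₀ = 0.50 and p₁ = 0.75 this is 30.35, rounded up to 31; twice 31 is 62, as stated. Attendance (33% against 60%) gives 26.9, or 30.5 with a continuity correction, which also rounds up to 31. The sample size is thus reproduced, but it does not show whether retention was meant to be judged per arm. With 0.70 in place of 0.75, the retention formula gives 49.7, or 50.

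**2. 70% cutoff, one proportion, 31 per arm.** 0.70 × 62 = 43.4, so 44 are needed. The largest count at or below 50% of 31 is 15.
- MSC-LC 15/31 = 48.4% and control 29/31 = 93.5%: 44/62 = 71.0%, *feasible*. The gap is 14/31 = 45 points, the smallest that produces this result.
- With control complete at 31/31, MSC-LC could be 13/31 = 41.9%.

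**3. 70% cutoff, 45 per arm.** 0.70 × 90 = 63. MSC-LC 22/45 (48.9%) and control 41/45 (91.1%) give 63/90 = 70.0%. The gap is 19/45 = 42 points.

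**4. 75% cutoff.** With equal arms the result is impossible: at most 15 + 31 = 46/62 = 74.2%, or 22 + 45 = 67/90 = 74.4%. It needs uneven arms and complete control retention, for example 15/30 + 32/32 = 47/62 = 75.8%.

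**5. How often (assumed true rates).** The documents give no retention data, so these are scenarios. Exact binomial, 31 per arm, 70% cutoff:

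| True MSC-LC / control | Pooled rule says *feasible* | ...and MSC-LC observed at or below 50% |
|---|---|---|
| 50% / 95% | 68.6% | 19.8% |
| 50% / 90% | 49.2% | 7.9% |
| 55% / 90% | 67.7% | 5.7% |
| 60% / 85% | 67.2% | 1.0% |
| 70% / 90% | 97.4% | 0.3% |

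**6. Cost of two possible repairs.** Chance of *feasible* at 31 per arm when both arms have the same true retention:

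| True retention | Pooled 70% | Pooled 70% plus 50% floor per arm | 70% required in each arm (22/31) |
|---|---|---|---|
| 70% | 49.6% | 49.6% | 29.3% |
| 75% | 81.2% | 81.2% | 59.4% |

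At true rates of 50% and 90% the floor lowers the chance of *feasible* from 49.2% to 41.3%.

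**The case against.** A reader might infer that the whole trial could be declared feasible while the MSC-LC arm fails. The documents do not support that. Retention is one of several criteria, and MSC-LC has its own attendance criterion: at 31 participants, 0.60 × 31 = 18.6, so 19 must attend six or more sessions. In the example above only 15 remain at the post-intervention assessment, so attendance would also pass only if at least four such attenders were missing then. That is possible, since attendance and questionnaire completion are recorded separately, but it is not automatic. This objection stands and confines the point to the retention criterion.

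A reader might also infer that control retention will be high and will mask loss in MSC-LC. The documents do not show this. Payment per assessment is the same in both arms. MSC-LC participants get more reminders and follow-up contact, and those who miss more than five sessions are still invited to complete questionnaires. The imbalance could run either way, which is a reason for a symmetric safeguard rather than one for MSC-LC alone.

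Pooling is inferred. The article never says that the two arms are combined, and 31 per condition is compatible with judging each arm. This stands as a caution, but the unrestricted wording next to an attendance rule that does name its arm makes the pooled reading the natural one.

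Finally, the result needs an extreme gap and disappears with equal arms at 75%. Both are true. They limit the size of the problem, but 70% is the cutoff in the analysis section and in the aims.

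**Conclusion.** The point holds in a limited form. Read as one proportion with the 70% cutoff, the retention criterion can be classed *feasible* while one arm is at or below the 50% line that the plan itself treats as *not feasible*. This takes a gap of about 42 to 45 points or more, with the better arm at about 91 to 94% or above. Under the assumed scenarios, the chance of it occurring with MSC-LC as the weaker arm runs from 0.3% to about 20% at 31 per arm. The conclusion rests on the pooled reading and on 70% rather than 75% being the operative cutoff; the article contradicts itself on the second. It says nothing about the attendance criterion or about an overall decision on the trial.

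**What to change.** Keep the overall retention cutoff and state that it is computed over both arms. Add one condition: retention cannot be classed *feasible* if either arm is at or below 50% at the post-intervention assessment. Report retention by arm, with the between-arm difference and its 95% CI. In the same edit, reconcile 70% (aims and Quantitative analyses) with 75% (Sample size justification), and make the assessment to which the cutoff refers the same in each place.

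No new data are needed. The arm-level figures rest on about 31 people each and will be imprecise. With equal true retention of 70% or more the floor leaves the chance of passing essentially unchanged. It is a safeguard against the observed contradiction, not a sensitive test: at true rates of 50% and 90% the criterion would still pass about 41% of the time, so the between-arm difference must be read alongside it. Requiring 70% in each arm would detect more, but it is a materially stricter rule (29% against 50% chance of passing at a true 70% in both arms), and adopting it would be a design choice rather than a correction.
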